## Study Procedures

## Randomization and blinding

Participants will be randomized through REDCap using stratified assignment based on biological sex and age (65-72 and 73+) to maintain equal representation of older vs. younger males and females in each group. Once randomized, patients will be informed of their assigned condition, and their study visits will be scheduled. Both participants and the research staff who conduct the assessments will not be blinded to the participants’ treatment assignments. Secondary coders that review videos weekly to assess quality and for safety control will be blinded.

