**Daily exercise performance**

Participants will enter their push-up, chair stand, row and step-up exercise repetitions, whether they used exercise modifications, and how difficult they felt the workout was using a survey sent daily through REDCap.

Videos will be reviewed weekly by a blinded secondary coder to measure quality and safety control for the exercises performed. All timed outcome measure performances will be immediately recorded during the Zoom session at the conclusion of each functional performance measure and re-evaluated offline by a blinded reviewer. Discrepancies in recorded times that are greater than one second will be replaced with the time recorded by the secondary reviewer. If discrepancies in recorded times are less than 1 second, the average of the two values will be used. If there is a disagreement on the number of repetitions performed between the blinded secondary coder and the unblinded research staff member conducting the exercise session, the blinded staff member will provide the final adjudication.

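### The two timed primary outcomes (FTSTS and OLST) keep half of any sub-second lean by the unblinded assessor, although a blinded reading of every timed test already exists

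*Protocol*

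**What the plan says.** The Protocol's Randomization and blinding section states: "Both participants and the research staff who conduct the assessments will not be blinded to the participants’ treatment assignments". The Daily exercise performance section has timed outcomes recorded live in the Zoom session and then "re-evaluated offline by a blinded reviewer". It combines the two readings as follows:

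- Gap above 1 second: "Discrepancies in recorded times that are greater than one second will be replaced with the time recorded by the secondary reviewer".
- Gap below 1 second: "If discrepancies in recorded times are less than 1 second, the average of the two values will be used".
- Gap of exactly 1 second: no rule.
- Disagreement on repetitions: "the blinded staff member will provide the final adjudication".

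Primary Study Endpoints lists four measures. FTSTS and OLST are times, the 30-second chair test is a count, and daily exercise performance is self-reported. The timing rule reaches only the first two.

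On the coders, Randomization and blinding says: "Secondary coders that review videos weekly to assess quality and for safety control will be blinded". Daily exercise performance adds: "Videos will be reviewed weekly by a blinded secondary coder to measure quality and safety control for the exercises performed". The Coaching section places Zoom sessions at baseline and weeks 2, 4 and 8. Under Delayed intervention control, controls have usual care until their 12-week follow-up is complete.

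**The concern.** FTSTS and OLST are stopwatch measures in an open-label trial, which is presumably why the protocol pays for a blinded re-reading. The combining rule then gives up part of that benefit. It removes large, conspicuous discrepancies but gives the unblinded reading 50% weight when the discrepancy is small. A slightly early or late stopwatch press by someone who knows the arm would fall in that range. Averaging reduces random error but cannot remove a lean in one direction. The same paragraph lets the blinded reader settle repetition disagreements, and gives no reason for treating times differently.

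This is not a detail left for a statistical analysis plan: the protocol itself fixes the rule. At stake is a small spurious contribution to the treatment effect on two primary outcomes.

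**Working it through.** **1. The plan's own figure.** Inputs from Sample size determination: d = 0.60, two-sided 0.05, 80% power, 20% attrition.

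n per group = 2 × (1.960 + 0.842)² / 0.60² = 43.6, so 44 per group and 88 in total. Then 88 / (1 − 0.20) = 110. The stated figures reproduce (power 0.804 at 44 per group). Nothing below changes them.

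**2. What the rule keeps.** Let D = live reading minus blinded reading. Then final value minus blinded value is:

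- D/2 if |D| < 1 s
- 0 if |D| > 1 s
- undefined if |D| = 1 s

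So the live reading can move any one recorded time by less than 0.5 s.

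**3. When this biases the comparison.** Statistical analysis uses mixed models with a group-by-time term. Write r for the mean retained shift in an arm at a visit. The bias in the change contrast is (r at week 12 − r at baseline) in the intervention arm, minus the same difference in the control arm. A lean common to both arms cancels. So does an arm-specific lean that is the same at every visit. Only a lean that differs by arm and arises after baseline remains.

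**4. Upper bound for a lean confined to one arm's follow-up readings.** Assume every intervention-arm follow-up reading is shifted by just under 1 s, with no shift in controls or at baseline. The bias is then 0.5 s. (An opposite lean in controls would add to it; none is assumed.) The SDs are assumptions. The type I error is for a simple two-group comparison with 44 per group: x = 0.5 / (SD × √(2/44)), error = 1 − Φ(1.96 − x) + Φ(−1.96 − x).

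| Assumed SD (s) | Bias in SD units | Share of d = 0.60 | Type I error |
|---|---|---|---|
| 2 | 0.25 | 42% | 0.22 |
| 3 | 0.17 | 28% | 0.12 |
| 4 | 0.125 | 21% | 0.09 |
| 5 | 0.10 | 17% | 0.08 |
| 10 | 0.05 | 8% | 0.06 |

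**5. With reading noise.** Let D be a constant lean plus normal noise. The noise SD is also assumed. Mean retained shift in seconds, by simulation:

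| Lean (s) | Noise SD 0.1 | Noise SD 0.3 | Noise SD 0.5 |
|---|---|---|---|
| 0.5 | 0.25 | 0.22 | 0.15 |
| 0.8 | 0.39 | 0.25 | 0.17 |
| 1.0 | 0.23 | 0.19 | 0.15 |
| 1.5 | 0.00 | 0.02 | 0.06 |

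For leans of 0.5 and 0.8 s and an outcome SD of 3 to 5 s, the bias runs from 0.15/5 = 0.03 SD to 0.39/3 = 0.13 SD. Type I error is about 0.05 to 0.09. Larger leans mostly trigger replacement and nearly vanish.

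**6. With the blinded time used throughout,** the retained shift from the live reading is 0 s and N is unchanged.

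**The case against.** Averaging two close readings is a recognisable way to reduce reading noise, and the rule limits the damage: gaps above 1 second are fully replaced. The condition in step 3 is demanding. Study visits are scheduled after allocation, so the assessor may know the arm at baseline too, and a constant lean would then cancel. The protocol gives neither an SD in seconds nor any evidence of a lean. All of this stands, and it keeps the point modest. It does not justify the rule, because the better reading is already collected.

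Two stronger readings are tempting, and the documents support neither.

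- *The blinded re-reading fails to protect the primary outcomes.* It does protect them in part. Only two of four primary measures are timed, and what they retain is capped. Repetition disagreements go to the blinded reader. That sentence speaks of an exercise session, so whether it covers the 30-second chair test could be worded more tightly.
- *The blinded coder is in fact unblinded by coaching videos.* During the 12 weeks only the intervention arm does the exercise programme, so a coder who saw those sessions could infer the arm. But the protocol does not say that coaching is recorded, which sessions supply the weekly videos, or that one person does both tasks. It refers to coders in the plural and calls them blinded. Controls also exercise after week 12, so a clip without timing need not reveal the arm.

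**Conclusion.** The point holds as an avoidable weakness in scoring the two timed outcomes. Below 1 second, half of the unblinded assessor's lean stays in FTSTS and OLST, always under 0.5 s per reading, and a gap of exactly 1 second is unassigned. At an assumed SD of 3 to 5 s the one-arm upper bound is about 0.10 to 0.17 SD, and the noisy cases worked here are smaller. These sizes rest on assumed SDs, assumed leans and the condition that the lean differs by arm and arises after baseline.

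A reader might simply halve a 0.8 s lean to 0.4 s and quote 13 to 22% of the planned effect (0.4/5 = 0.08 SD and 0.4/3 = 0.13 SD, each over 0.60). That supposes no reading noise and a lean near the 1-second limit. With the noise assumed above, 0.17 to 0.39 s remains. The role of the video coders is an open question to clarify, not a demonstrated breach of blinding.

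**What to change.** Replace the two timing rules with one: the blinded reviewer's time is the recorded value for every timed test, and the live reading is used only if the video is unusable. This matches the existing treatment of repetition disagreements and closes the gap at exactly 1 second. It costs one sentence, no extra readings and no change to 88 or 110. The downside is losing the slight noise reduction from averaging two readings.

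Add one clarifying sentence: outcome clips are scored by a coder who has not reviewed that participant's exercise-session videos, ideally from clips trimmed to the test and carrying no arm or visit label. This means reallocating existing coders and some light trimming.

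Neither change addresses how an unblinded assessor might encourage participants during a test; a re-reading cannot correct that.

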### Secondary Outcome Measure

### Adherence and retention

An exercise session will be determined to have been completed only if the participants complete the daily REDCap survey reporting their performance, exercise modification use and difficulty level.

If participants do not complete their daily exercise sessions for ≥ 3 days, research staff will attempt to contact the lapsed participants via phone and email up to 5 times to re-engage them. Participants will be contacted every 48 hours until 14 days of missed daily participation. Participants who do not respond to the project staff for ≥ 14 days will be treated as unable-to-be-contacted with no further contact attempts made unless the participant re-establishes contact on their own.

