## Sample size determination

Effect size calculations are based on evidence that 30 second chair stand performance declines with age and predicts future functional decline. We considered a large effect size as healthier patients in our pilot showed large gains (i.e., *d > 1.00)* in squat performance, but because our intended sample has at least some degree of limitations with walking, we expect a more conservative effect of the intervention on measures of physical function (i.e., d = .60).

Based on a 2-group design (intervention, control) assuming a moderate standardized between-group difference at 12 weeks (Cohen’s d = .60), a sample size of 88 (44 per group) would be needed to detect a difference between groups with a two-sided significance level of 0.05 and 80% power. To account for an anticipated 20% attrition rate over the study period, we will recruit up to 110 participants.

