## Statistical analysis

Summary statistics (e.g., mean and standard deviation (SD) for continuous variables; frequency and proportion for categorical variables) will be reported for participant baseline characteristics. Baseline differences between randomly assigned participants will be evaluated with two-sample t-tests and Fisher’s exact tests. Changes in the primary outcome measures over 12 weeks will be evaluated at the group level using linear mixed-effect models to analyze change over time and the Group x Time interaction. The analysis will employ an intention-to-treat approach, with missing data addressed through mixed-effects modeling in the longitudinal data analysis framework. A two-sided *p*-value of less than or equal to .05 will be considered statistically significant.

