### Criteria for removal from study

Participants may be from the study if they become injured and cannot exercise or if they are asked by their Primary Care Provider to suspend exercise. The Principal Investigator reserves the right to remove a participant from the study for any reason, based on their discretion, particularly a belief that continued participation exposes them to unnecessary risk. Also, participants have the right to withdraw themselves at any time and halt all study-related activities permanently.

Other withdrawal criteria include: unwillingness to follow protocol during visits, unwillingness to complete study visits, and/or return of equipment to study staff, withdrawal of consent by the participant, development of a new medical problem that would exclude them from the study.

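### The contact and removal rules can end outcome follow-up differentially in the intervention arm, which the intention-to-treat mixed model repairs only if the losses are missing at random

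*Protocol*

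**What the plan says.** Four parts of the protocol bear on this point.

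- **Adherence and retention.** Three or more days of missed daily sessions start re-engagement by phone and email, with up to 5 attempts. People who then do not respond for 14 days or more are "treated as unable-to-be-contacted with no further contact attempts made unless the participant re-establishes contact on their own".
- **Delayed intervention control.** Controls stay on usual care and start daily exercise only after the 12-week follow-up.
- **Criteria for removal from study.** Participants may be removed "if they become injured and cannot exercise or if they are asked by their Primary Care Provider to suspend exercise". Other grounds include "unwillingness to follow protocol during visits, unwillingness to complete study visits", investigator discretion, withdrawal of consent and a new medical problem.
- **Statistical analysis.** "The analysis will employ an intention-to-treat approach, with missing data addressed through mixed-effects modeling".

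Functional Performance Measures schedules the tests for both groups at baseline, week 6 and week 12. It does not say whether someone who has lapsed, become uncontactable or been removed is still invited.

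**The concern.** An intention-to-treat comparison needs outcomes sought from everyone randomised, whether or not they exercise. Here the event that can end contact starts with non-adherence to the assigned exercise, and only one arm has exercise to adhere to. The cut-off is worded as an end to contact altogether, not just to adherence reminders. The two exercise-linked removal grounds work in the same direction, because they lead out of the study and not only out of the programme.

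The outcomes are tests of leg strength and balance. People who stop training or are injured are plausibly those with the least gain. If they are lost mainly from the intervention arm, the model predicts their week 12 values from intervention participants who stayed. The estimate then moves toward the effect in people who kept exercising.

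This is a data-collection rule. A SAP (not available for this review) could add sensitivity analyses, but it could not recover assessments that were never attempted.

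**Working it through.** **1. The plan's own figures.** Inputs from Sample size determination: d = 0.60, "with a two-sided significance level of 0.05 and 80% power", and "a sample size of 88 (44 per group) would be needed to detect a difference between groups".

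- Normal approximation: n per arm = 2 × (1.960 + 0.842)² / 0.60² = 43.6, so 44 per arm and 88 in total. This reproduces. The exact t-test needs 44.6, so 45 per arm; at 44 per arm its power is 79.5%.
- Attrition: 88 / (1 − 0.20) = 110. This reproduces.

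The allowance protects precision only, and the protocol does not split it by arm. It covers 110 − 88 = 22 losses. If all 22 fell in the intervention arm, that would be 22/55 = 40% of it. Power at 33 v 55 and d = 0.60 would still be about 77%. The issue is bias, not sample size.

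**2. Who the rules reach.**

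| Rule | Intervention arm | Control arm, weeks 0 to 12 |
|---|---|---|
| Missed sessions, then 14 days of non-response | Can arise | Cannot arise: no sessions assigned |
| Injury preventing exercise; provider asks to suspend exercise | Can arise | Little occasion in practice |
| Discretion, visit refusal, consent withdrawal, new medical problem | Can arise | Can arise |

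Timing matters too. A participant who lapses at day 21, is first contacted at day 24 and stays silent for 14 days is cut off at day 38, before week 6 (day 42). That person contributes only a baseline value.

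**3. Size of the bias.** Let f be the fraction of the intervention arm lost, gS the effect in stayers and gL the effect in lapsers at week 12, both in SD units. Assume no loss in controls.

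- Effect of assignment = (1 − f) × gS + f × gL
- Estimate when lapsers are predicted from stayers ≈ gS
- Bias = f × (gS − gL)

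Take gS = 0.60. The values of f and gL are assumptions; the protocol gives neither.

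| f | True effect, no gain kept | Bias, no gain kept | Bias, half kept | Bias, all kept |
|---|---|---|---|---|
| 10% | 0.54 | +0.06 | +0.03 | 0 |
| 20% | 0.48 | +0.12 | +0.06 | 0 |
| 30% | 0.42 | +0.18 | +0.09 | 0 |
| 40% | 0.36 | +0.24 | +0.12 | 0 |

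**4. Does the mixed model rescue it?** A simulation of baseline, week 6 and week 12 used a missing-at-random analysis by sequential regression. It assumed a correlation of 0.7 between visits and stayers' gains of 0.30 SD at week 6 and 0.60 SD at week 12. With 20% loss and no gain kept:

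- Lost before week 6: estimate about 0.60 against a true 0.48, bias +0.12.
- Lost after week 6, with the gain not yet lost at week 6: the same, +0.12.
- Lost after week 6, with the missing gain already visible at week 6: estimate about 0.58, bias about +0.10.

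Making lapse depend on baseline did not change these results. The model removes the part that observed data predict and leaves the rest.

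**5. Under no treatment effect.** Suppose lapsers are 0.5 SD worse than stayers in a way the model cannot predict. Then 20% loss gives a spurious 0.20 × 0.5 = 0.10 SD and a type I error of about 8%. At 40% loss these become 0.20 SD and about 15%.

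**The case against.** The other side has a good deal to say, and most of it limits the point.

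- **Stopping exercise is not enough to be cut off.** A reader might infer that the 14-day rule drops anyone who stops exercising. It does not: it needs 14 days of non-response as well. Someone who lapses but answers staff stays in contact, and many who ignore every approach would be lost under any rule. This stands.
- **Removal is permissive and partly common to both arms.** The text says participants may be removed, and several grounds apply equally to controls. The grounds about unwillingness concern visits and return of equipment, not failure to exercise daily. So it cannot be said that all such losses fall in the intervention arm. This stands.
- **A mixed model with missing outcomes can still be intention-to-treat.** A reader might infer that the result would not be intention-to-treat. The documents do not support that: participants can be analysed as randomised with whatever data they have. What is at risk is the estimate of the effect of assignment if losses are not missing at random. This stands.
- **Bias toward benefit is not established.** The protocol gives no loss rate by arm and no outcome for lapsers. Its 0.60 is a planned between-group difference, not an effect in adherers. Informative loss among controls could offset the bias. This stands, so the range has to include 0.
- **Some tests may not be possible** in people who are injured or whose provider has suspended exercise. This also stands, and it limits what the fix can recover.

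None of this supplies a provision that keeps lapsed or removed participants in the week 6 and week 12 assessments, or a matching contact rule for controls.

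**Conclusion.** The point holds in a limited form. As written, one contact rule can end follow-up only in the intervention arm during the 12 weeks, two removal grounds are tied to exercise, and no safeguard keeps those affected in outcome assessment. This sits badly with the intention-to-treat aim, because the planned analysis then depends on missing at random exactly where that assumption is least secure.

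The size is uncertain. With 20% of the intervention arm lost and a gain of 0.60 SD in stayers, the bias runs from 0 to about +0.12 SD, depending on what lapsers retain. Across 10 to 40% loss with no gain retained, it is up to +0.06 to +0.24 SD, somewhat less where the missing gain already shows at week 6. These figures rest on assumed loss confined to one arm and assumed lapser outcomes. The direction is probably toward benefit, but that is a judgement and not something the protocol shows.

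**What to change.** 1. **Adherence and retention:** limit the 14-day cut-off to contacts about exercise adherence. State that every randomised participant is still invited to the week 6 and week 12 assessments, with the same number of attempts in both arms, unless consent for follow-up is withdrawn.
2. **Criteria for removal from study:** separate discontinuing the exercise programme from leaving outcome follow-up. When a test cannot be done, record the reason.
3. **Statistical analysis:** keep all randomised participants in the analysis as assigned. A missing-not-at-random sensitivity analysis is a useful companion and can sit in the SAP.

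Clinical decisions on stopping exercise, and on whether a test can be performed, are unchanged.

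The cost is protocol wording and a few extra scheduling contacts. The observed effect may be smaller: with 55 per arm fully followed and a true effect of 0.48, power is about 70%. Some non-responders and injured participants will still have missing values.

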## Sample size determination

Effect size calculations are based on evidence that 30 second chair stand performance declines with age and predicts future functional decline. We considered a large effect size as healthier patients in our pilot showed large gains (i.e., *d > 1.00)* in squat performance, but because our intended sample has at least some degree of limitations with walking, we expect a more conservative effect of the intervention on measures of physical function (i.e., d = .60).

Based on a 2-group design (intervention, control) assuming a moderate standardized between-group difference at 12 weeks (Cohen’s d = .60), a sample size of 88 (44 per group) would be needed to detect a difference between groups with a two-sided significance level of 0.05 and 80% power. To account for an anticipated 20% attrition rate over the study period, we will recruit up to 110 participants.

## Statistical analysis

Summary statistics (e.g., mean and standard deviation (SD) for continuous variables; frequency and proportion for categorical variables) will be reported for participant baseline characteristics. Baseline differences between randomly assigned participants will be evaluated with two-sample t-tests and Fisher’s exact tests. Changes in the primary outcome measures over 12 weeks will be evaluated at the group level using linear mixed-effect models to analyze change over time and the Group x Time interaction. The analysis will employ an intention-to-treat approach, with missing data addressed through mixed-effects modeling in the longitudinal data analysis framework. A two-sided *p*-value of less than or equal to .05 will be considered statistically significant.

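### The trial is sized on a 12-week group difference, but the planned Group x Time test is not tied to a week-12 contrast; a baseline-adjusted week-12 comparison would answer the sized question more precisely at no cost

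*Protocol*

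**What the plan says.** **Sizing.** The Sample size determination section works from a two-group design, "assuming a moderate standardized between-group difference at 12 weeks" with d = 0.60. It concludes that "a sample size of 88 (44 per group) would be needed" for a "two-sided significance level of 0.05 and 80% power", and raises this to 110 for 20% attrition. It does not say whether d is standardised by the SD at week 12 or by the SD of change.

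**Analysis.** The Statistical analysis section evaluates changes in the primary outcomes over 12 weeks "using linear mixed-effect models to analyze change over time and the Group x Time interaction". It does not say whether time is linear or categorical, or whether the deciding test is one week-12 term or the overall interaction. It names no baseline adjustment and no covariates, and excludes neither. It adds that "Baseline differences between randomly assigned participants will be evaluated with two-sample t-tests and Fisher’s exact tests".

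**Related text.** The Study Hypothesis section speaks of improvement in 12 weeks relative to the delayed-treatment control. The functional measures are taken at baseline, week 6 and week 12. The Randomization and blinding section stratifies by sex and by age (65-72, 73+).

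**The concern.** The power statement and the analysis statement should describe the same test, and here nothing links them. The analysis sentence has at least three readings:

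- **Overall interaction, categorical time.** With three visits this has 2 degrees of freedom. It can be significant because the arms differ at week 6 and not at week 12, so a positive result would not by itself support a claim about 12 weeks.
- **Week-12 interaction term, categorical time.** This is the between-group difference in change from baseline to week 12. It answers the right question, but if baseline is left unconstrained it carries the full baseline noise.
- **Slope, linear time.** This answers the question only if change is close to a straight line.

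If the contrast is not named before the data are seen, the choice could be made afterwards. The change contrast also gives up precision that baseline data already being collected would provide.

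**Working it through.** **Inputs from the protocol:** d = 0.60 at week 12, 44 per arm, two-sided 0.05, 80% power, 20% attrition, three visits.

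**Assumed, because the protocol gives no figure:** equal SD at each visit, d in week-12 SD units, and a correlation ρ between any two visits (compound symmetry), varied from 0.3 to 0.8. Data are taken as complete for 44 per arm.

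**Step 1, the plan's own figure.** n per arm = 2(1.960 + 0.842)² / 0.60² = 43.6, rounded up to 44, so 88 in total; 88 / 0.80 = 110. Power at 44 per arm is 80.4% by the normal approximation and 79.5% by the noncentral t. The plan's numbers reproduce, and they are those of a two-group comparison of means at one time.

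**Step 2, 12-week change contrast.** Its variance is 2(1 − ρ) times the week-12 variance, so the effective effect is 0.60/√(2(1 − ρ)). At ρ = 0.3 this is 0.60/1.183 = 0.507; at 0.5 it is 0.600; at 0.7 it is 0.60/0.775 = 0.775. Power is from the noncentral t with 86 df.

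**Step 3, baseline-adjusted week-12 contrast.** Its variance is (1 − ρ²) times the week-12 variance, so the effective effect is 0.60/√(1 − ρ²): 0.629, 0.693 and 0.840 at the same ρ. The variance ratio of change to adjusted is 2(1 − ρ)/(1 − ρ²) = 2/(1 + ρ), which exceeds 1 for every ρ below 1. The adjusted contrast is therefore always the more precise of the two.

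**Step 4, overall 2-df interaction.** With effects d6 at week 6 and d12 at week 12, the noncentrality is λ = 22 × 2(d6² − d6·d12 + d12²) / (3(1 − ρ)), referred to a noncentral F(2, 86). For fixed d12 the bracket is smallest at d6 = d12/2, so half the effect at week 6 is the least favourable case. At ρ = 0.5:

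- d6 = 0.30: λ = 22 × 2 × 0.27 / 1.5 = 7.92.
- d6 = 0 or 0.60: λ = 22 × 2 × 0.36 / 1.5 = 10.56.

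| ρ (assumed) | 12-week change, 1 df | Baseline-adjusted week 12, 1 df | 2-df, half the effect at week 6 | 2-df, full effect or none at week 6 |
|---|---|---|---|---|
| 0.3 | 65% | 83% | 54% | 67% |
| 0.5 | 79% | 89% | 70% | 82% |
| 0.6 | 88% | 94% | 80% | 90% |
| 0.7 | 95% | 97% | 90% | 97% |
| 0.8 | 99% | 99.6% | 98% | 99.7% |

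**Step 5, week 6 alone.** With d6 = 0.60 and d12 = 0 the bracket is again 0.36, so at ρ = 0.5 the 2-df test is significant 82% of the time although the arms do not differ at week 12.

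**Step 6, the other reading of d.** If 0.60 is in change-SD units, the effective effect in Step 2 is 0.60 whatever ρ is, and the change contrast has the power found in Step 1.

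**Step 7, strata.** If sex and age group explained an assumed 2%, 5% or 10% of week-12 variance, the power of the plain week-12 comparison would move from 80.4% to 81.1%, 82.3% or 84.3% (normal approximation).

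**The case against.** **The analysis text may already mean the week-12 contrast.** It refers to change over 12 weeks, and with categorical time one interaction term is exactly the 12-week difference in change. This stands: the plan leaves the contrast unnamed and does not contradict the sizing.

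**Model detail belongs in the SAP.** Time coding, baseline handling and covariates are commonly left to that document, which is not at hand. Their absence from the protocol is no error. What remains is that the protocol itself fixes both a sizing basis and a test, and does not connect them.

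**The trial is underpowered.** A reader might infer this from the low entries in the table. The documents do not support it. They give neither ρ nor the SD behind d, the low entries need a low ρ, and the 54% to 80% run in the 2-df column also needs the least favourable week-6 effect. The d was scaled down from pilot gains in squat performance, so a change-based reading is open.

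**Leaving out the strata inflates the standard error.** A reader might infer this too. It applies to comparisons between persons. In a within-person Group x Time contrast with complete data, main effects of sex and age cancel. Nor did the stated 80% assume covariates.

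**The baseline tests are used to correct imbalance.** The protocol does not say so; it says only that differences will be evaluated.

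**Conclusion.** The point holds as an unlinked test and a missed gain in precision. The sizing is for a group difference at 12 weeks, while the named test is an interaction over three visits with no stated contrast. One natural reading, the 2-df test, can be significant without any week-12 effect.

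The baseline-adjusted week-12 contrast beats the 12-week change contrast at every correlation examined: by 18 percentage points of power at ρ = 0.3, 10 at 0.5 and 2 at 0.7. At ρ = 0.5, 80% power needs 44 per arm for the change contrast and 33 for the adjusted one (normal approximation). These sizes rest on an assumed ρ, d in week-12 SD units, equal SDs and complete data on 44 per arm. The direction of the comparison does not depend on ρ.

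The stated 80% is not shown to be wrong. The change contrast meets it at ρ of about 0.5 or more, or at any ρ if d is in change-SD units.

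**What to change.** In the Statistical analysis section:

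- For the functional measures, make the primary test the 1-df between-group difference at week 12, from the same mixed model with categorical time.
- Adjust for the baseline value. Use it as a covariate, or constrain the baseline means to be equal if baseline is measured before allocation is known. The Randomization and blinding section has visits scheduled after participants learn their assignment, so this condition should be checked first.
- Include the randomisation strata (sex; age 65-72 or 73+) as fixed effects. The added gain is probably small.
- Keep the overall Group x Time interaction as descriptive.

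In the Sample size determination section, state which SD d = 0.60 refers to.

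Dropping the baseline significance tests and keeping the summary table is sound reporting advice, but does not affect the primary inference.

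The cost is about one paragraph of text, with no new data, visits or participants.
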